**Enrollment**								
**Eligibility screen**	X							
**Informed consent**	X							
**History information**	X							
**Baseline testing**	X							
**Allocation**		X						
**Interventions**								
***Secondary in-the-bag IOL implantation***		X						
***Secondary ciliary sulcus IOL implantation***		X						
**Assessments**								
***Vital signs***	X	X	X	X	X	X	etc	X
***Systemic examinations***		X						
***Visual acuity***	X	X		X	X	X	etc	X
***Ocular refractive power***	X	X			X	X	etc	X
***Intraocular pressure***	X	X		X	X	X	etc	X
***Slit lamp***	X	X		X	X	X	etc	X
***Cornea endothelium count***		X			X	X	etc	X
***Ocular biological measurement***		X			X	X	etc	X
***Slit-lamp photography***		X		X	X	X	etc	X
***Pentacam***		X			X	X	etc	X
***CASIA2***		X			X	X	etc	X
***Fundus photography***		X			X	X	etc	X
***Optical coherence tomography***		X			X	X	etc	X

### Sample size

According to the Zhongshan Ophthalmic Center’s outpatient record system, (1) the one-year incidence of glaucoma-related AEs in sulcus implantation is 12%. Assuming the in-the-bag implantation would reduce the absolute incidence to 0.7%, to achieve 90% power with a two-sided alpha of 0.0492 (the interim analysis at 6 months postoperatively spending alpha of 0.0054 by O’Brien-Fleming approach), 114 eyes are needed for each group (total of 228 eyes) using Fisher’s exact test with pooled variance. Allowing for a 20% loss to follow-up, 143 eyes should be needed in each group. Assumptions: % of bilateral = 75%, inter-eye correlation among bilateral patients = 0.5. For bilateral patients, two eyes have the same type of surgery. The number of patients (*X*) per group can be calculated by solving the following equation: *X* × 0.75 × 2/(1 + 0.5) + *X* × 0.25 = 143, *X* = 114 patients per group, a total of 228 patients. The sample size is calculated by PASS 16.0 (NCSS, LLC, USA). (2) IOL decentration in 3-dimension in the capsular group is 0.38 mm while in the sulcus group, it is 0.56 mm. Group sample sizes of 106 and 106 achieve 90% power to detect the mean difference of 0.18 between two trial arms with a common standard deviation for both groups of 0.40 and with a two-sided alpha of 0.0492 using a two-sided two-sample equal-variance *t*-test (same interim analysis as above for the 1-year incidence of glaucoma-related AEs). Allowing for a 20% loss to follow-up, 133 eyes should be needed in each group. Assumptions: % of bilateral = 75%, inter-eye correlation among bilateral patients = 0.5. For bilateral patients, two eyes have the same type of surgery. The number of patients (*X*) per group can be calculated by solving the following equation: *X* × 0.75 × 2/(1 + 0.5) + *X* × 0.25 = 133, *X* = 106 patients per group, a total of 212 patients. The sample size is calculated by PASS 16.0.

Considering the sample size calculated by the two primary outcomes, the largest one is selected: 114 patients per group, a total of 228 patients.

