### Outcomes

#### Primary outcomes

The primary outcomes include IOL decentration and the incidence of glaucoma-related AEs by 1 year postoperatively.Glaucoma-related AEs are defined using the Infant Aphakia Treatment Study: “comprising ocular hypertension, pupil block, and glaucoma” [19].Ocular hypertension is defined as intraocular pressure (IOP) ≥ 21 mm Hg.Transient ocular hypertension is defined as elevated IOP which is resolved with cessation of topical steroids. Cases which do not resolve are classified as persistent ocular hypertension.Pupil block is defined as ocular hypertension in the context of a history of obstruction of aqueous flow through the pupil.Glaucoma is defined using the 2001 British Infantile and Childhood Glaucoma (“BIG eye”) study group taxonomy: “the presence of a combination (more than one) of clinical signs consistent with high intraocular pressure (≥ 21 mmHg), such as high pressure, optic disc cupping ≥ 0.3 or disc asymmetry ≥ 0.2, progressive disc cupping, buphthalmos, enlarged corneal diameter, corneal edema, Descemet’s membrane splits/Haab’s striae, visual field defects, or progressive myopia.IOL decentration will be measured using anterior segment optical coherence tomography (AS-OCT, CASIA2, Tomey Corporation, Japan) or Scheimpflug tomography (Pentacam HR 70900, Oculus GMbH, Germany) as previously described [21]. The details can be found in the “Testing procedures” section.

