### Statistical analysis

#### Statistical methods

The normality of continuous data is to be checked using the Shapiro–Wilk test and histogram. Continuous data are to be summarized as the mean ± standard deviation, median, or interquantile range (IQR). Analysis of the primary and secondary outcomes is to be based on the intention-to-treat (ITT) and per-protocol (PP) analyses, and missing data will be imputed by multiple imputation or other appropriate methods. In the ITT analysis, participants are evaluated on the basis of the group to which they were randomly assigned, regardless of whether they actually received the surgery. In the PP analysis, participants are evaluated on the basis of the group to which they actually received the surgery to truly reflect the difference between the two groups. Paired *t* test will be used to compare pre- vs. postoperative visual acuity (in logMAR), spherical equivalent aberration, IOL tilt, and decentration at each time point after surgery. Comparison between the two treatment groups will be performed using a mixed model for continuous outcomes and a generalized estimated equation (GEE) model for categorical outcomes. The incidence of glaucoma-related AEs (primary outcome) by 1 year will be compared using the *χ*^2^ test or Fisher’s exact test. Kaplan–Meier survival curves are to be constructed to show the cumulative probability of glaucoma-related AEs over time in each group, and the log-rank test is used to compare the time to incidence of glaucoma-related AEs between the two study groups. Unadjusted and adjusted hazard ratio (HR) of glaucoma-related AEs and 95% CIs will be estimated by univariable and multivariable Cox proportional hazards model, respectively. Study group, stratification variable (laterality), and other baseline variables with *P* < 0.20 in the univariable analysis will be included in the multivariable model. The inter-eye correlation will be adjusted for all analyses including both eyes from the same subject.

A two-sided *p* < 0.0054 for interim analysis and *p* < 0.0492 for the primary analysis is considered to be statistically significant. All statistical analysis will be performed using Stata 16 (StataCorp, College Station, TX, USA) and other appropriate software.

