#### Interim analyses

We plan to perform one interim analysis at 6 months postoperatively in the intention-to-treat population, up to half of the objective samples.

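### The interim and final thresholds 0.0054 and 0.0492 spend about 0.0513 two-sided at a half-way look, slightly more than the 0.05 they imply

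*Protocol article*

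**What the plan says.** Four places in the protocol article fix the rule.

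- **Sample size** plans the glaucoma-related outcome "to achieve 90% power with a two-sided alpha of 0.0492", with "the interim analysis at 6 months postoperatively spending alpha of 0.0054 by" O'Brien-Fleming. The same interim arrangement is applied to IOL decentration.
- **Statistical methods** turns both levels into decision thresholds: "0.0054 for interim analysis and" a final level of "0.0492 for the primary analysis is considered to be statistically significant".
- **Interim analyses** gives the timing and the amount of data: "We plan to perform one interim analysis at 6 months postoperatively in the intention-to-treat population, up to half of the objective samples".
- **Primary outcomes** sets the time point: "The primary outcomes include IOL decentration and the incidence of glaucoma-related AEs by 1 year postoperatively". The 6-month versions of both outcomes are listed under Secondary outcomes.

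No section states the overall type I error. A final level of 0.0492 with a small interim level points to 0.05, and that is the reading used here.

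**The concern.** The final level was lowered from 0.05 to pay for the interim test. If the reduction is too small, a final p-value that falls between the correct level and 0.0492 would be called significant without the intended protection.

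There is a second, related point. O'Brien-Fleming levels assume one outcome accumulating information, with a known correlation between the two test statistics. A look at 6 months, in at most half the sample, need not have that correlation with a test of 1-year outcomes. A weaker correlation raises the total.

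**Working it through.** **Inputs.** Interim level 0.0054 and final level 0.0492, two-sided (Sample size; Statistical methods). Information at the look: at most one half (Interim analyses). Overall target 0.05 (assumed, as above).

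**Step 1. Shape of the pair.** The critical values are z1 = 2.782 and z2 = 1.967. Their ratio is 1.4145, against √2 = 1.4142. This is the O'Brien-Fleming shape for a look at half information.

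**Step 2. What the pair spends.** With (Z1, Z2) bivariate normal and correlation √t at information fraction t, overall alpha = 1 − P(|Z1| < 2.782, |Z2| < 1.967). At t = 0.5 the correlation is 0.707 and the result is 0.0513. Letting both levels vary within their rounding limits gives 0.0512 to 0.0514, so rounding does not explain the gap.

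**Step 3. What 0.05 requires at t = 0.5.**

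| Rule | Interim | Final |
|---|---|---|
| Classical O'Brien-Fleming (constant 1.977) | 0.0052 | 0.0480 |
| Lan-DeMets, twice one-sided 0.025 | 0.0031 | 0.0490 |
| Lan-DeMets, spending function applied to 0.05 | 0.0056 | 0.0478 |
| Interim kept at 0.0054 | 0.0054 | 0.0479 |

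None of these gives 0.0054/0.0492. The stated pair holds 0.05 only from t of about 0.70 upward (correlation about 0.84), which "up to half of the objective samples" excludes.

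**Step 4. Less information, same outcome.** Total alpha is 0.0520 at t = 0.4 and 0.0526 at t = 0.3.

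**Step 5. A 6-month outcome at the look, half the sample.** The correlation of the two statistics becomes r × √0.5, where r is the correlation between the 6-month and 1-year outcomes. The documents do not give r.

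| Assumed r | Total alpha |
|---|---|
| 0.9 | 0.0519 |
| 0.8 | 0.0525 |
| 0.7 | 0.0529 |
| 0.5 | 0.0536 |
| 0 | 0.0543 |

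The last row is the maximum: 1 − (1 − 0.0054)(1 − 0.0492) = 0.0543. As a guide for a cumulative incidence, take a pooled 1-year rate of (12% + 0.7%)/2 = 6.35% and suppose half the events occur by 6 months. Then r = √[0.03175 × 0.9365 / (0.0635 × 0.96825)] = 0.70.

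**Step 6. Exact size for the binary outcome.** Taking 57 and then 114 independent eyes per group, the same outcome at both looks and the stated thresholds:

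| Null event rate | Fisher's exact | χ² |
|---|---|---|
| 5% | 0.021 | 0.046 |
| 6.35% | 0.023 | 0.048 |
| 12% | 0.030 | 0.051 |

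**Step 7. Sample size.** The plan's figures reproduce at 0.0492: 114 eyes per group from the pooled-variance formula with continuity correction, and 106 from the noncentral t (difference 0.18, SD 0.40, power 90.2%). Dividing by 0.8 gives 143 and 133. At 0.0480 both stay at 114 and 106, with decentration power at 106 per group of 90.0%. At 0.0446 they become 116 and 108 (145 and 135 after loss). Decentration power at 0.0446 is 89.5% with 106 per group and 91.5% with 114.

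**The case against.** The strongest reply is that little is at stake. The certain excess is 0.0513 − 0.05 = 0.0013, the target of 0.05 is inferred, and against the 0.0480 rule a conclusion changes only if the final p-value lies between 0.0480 and 0.0492. All of that stands and limits the weight of the point. It does not make the pair correct, because these are the operative thresholds and the rule they are attributed to gives different numbers.

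A reader might infer four stronger things that the documents do not support.

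- *The levels are not O'Brien-Fleming at all.* Their ratio is √2. Only the constant is off for an overall 0.05.
- *Both primary outcomes exceed 5%.* Step 6 shows Fisher's exact test well below 0.05 and χ² between 0.046 and 0.051. That calculation treats eyes as independent, so it leaves out the planned inter-eye adjustment, but it is enough to say that the nominal excess matters mainly for decentration.
- *Interim alpha is definitely spent on a secondary outcome.* The text says when the look happens, not which outcome it tests. A 6-month outcome is the natural reading, and a fuller document may settle it.
- *The true error is near 0.054.* That needs almost no correlation between 6 months and 1 year. A cumulative incidence includes every 6-month event, and decentration is measured repeatedly on the same lens, so near-zero values are implausible.

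Nor is the trial too small for this reason: the eye counts are unchanged at 0.0480.

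**Conclusion.** Wrong as written, with a small effect. For an overall two-sided 0.05 and a look at half information, 0.0054/0.0492 spends 0.0513. With less information, or with 6-month outcomes at the look, the nominal total is about 0.052 to 0.053 for r between 0.7 and 0.9, and cannot exceed 0.0543. The direction of the second effect is certain if the outcomes differ; its size rests on an r that the documents do not give. All these totals are normal-theory figures for each primary outcome separately, and they apply chiefly to IOL decentration. The defect concerns type I error control, not the sample size.

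**What to change.** State the overall two-sided alpha of 0.05 and the outcome tested at the look, then replace the pair in one of two ways.

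1. **Take the look when half the sample has 1-year outcomes, and use 0.0052/0.0480.** The stated 114 and 106 eyes per group do not change. The cost is a later look.
2. **Keep the look on 6-month outcomes at 0.0054, and use 0.05 − 0.0054 = 0.0446 at the final analysis.** This is valid at any correlation. Decentration power at 106 per group falls from 90.2% to 89.5%, and is 91.5% at the 114 that the trial is sized for. By the plan's own formula the stated sizes would become 116 and 108 eyes per group; after loss, 145/1.25 = 116 patients per group, or 232 instead of 228. For a change this small, restate the power and do not enrol more.

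Amend Sample size, Statistical methods and Interim analyses so that all three carry the same levels, outcome and timing. Apart from the timing of the look under the first option, this is a change of wording.

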### Recruitment

Consecutive potentially eligible participants will be identified in four eye clinics including ZOC, HNZOC, the First Affiliated Hospital of Guangxi Medical University, and Shenzhen Eye Hospital. Participants meeting the inclusion criteria will be enrolled in this study.

### Randomization

Stratified block randomization will be applied for this trial. The eligible participants stratified by site who consented will then be divided into two strata according to secondary intraocular lens implantation in the unilateral eyes or bilateral eyes. Participants in each stratum will be randomized (1:1) to receive the assigned treatment from either secondary in-the-bag IOL implantation or secondary sulcus IOL implantation. An independent statistician without involvement in the study will generate the randomization sequence for each stratum using an online randomization number generator (http://www.randomization.com).Study participants with one study eye will be randomly assigned to one of the treatment groups.Study participants with two study eyes (both eyes are eligible):If capsular surgery is applicable for both eyes, study participants will be randomly assigned to one of the treatment groups, and both eyes will receive the same treatment.If capsular surgery is applicable for only one eye, which will be randomly assigned to one of the treatment groups, the contralateral eye will receive sulcus surgery or other appropriate treatment.

### Masking

This is a single-blinded study, and participants are masked to the group assignment. Allocation codes are concealed before the secondary IOL implantation. Participating surgeons will be informed of the study group allocation just prior to the implantation of the IOL. The trial statistician who is responsible for the statistical analysis of the study is not involved in the assignment of treatments to participants. Research assistants determining participant eligibility, examiners, and outcome assessors cannot be masked to the group allocation because treatment can be identified from medical image.

### Data collection

Twenty-five visits including baseline visits over 10 years are planned, with follow-up examinations scheduled at 1 day, 1 week, 1 month, 3 months, 6 months, 12 months for the first year, and every 6 months thereafter.

Every time close to the scheduled visit, our research assistants will sincerely remind participants by text message or phone call. Besides, we offer a partial fee waiver for participant inspections.

#### History information

The following patient information will be collected: sex, age at secondary IOL implantation, age at the cataract extraction, laterality of IOL implantation, operation interval, systemic and ocular history, ocular and systemic comorbidities, and eye symptoms.

#### Baseline testing

All participants will be required to undergo systemic and ocular preoperative examinations. The assessment will be carried out by personnel who are masked to the study group assignment.Vital signsSystemic examinations: blood routine, biochemical tests, chest radiography, and electrocardiogramOcular examinations: visual acuity, ocular refractive power, intraocular pressure (IOP), slit lamp, cornea endothelium count, ocular biological measurement, slit-lamp photography, Pentacam, fundus photography, and optical coherence tomography

#### Testing procedures

##### Assessment of visual acuity

Visual acuity will be evaluated with an Early Treatment Diabetic Retinopathy Study (ETDRS) chart. For those who are unable to use the ETDRS chart, visual acuity is evaluated with Lea Symbol Chart or Teller Acuity Cards.

All decimal visual acuity outcomes will be converted to logarithm of the minimum angle of resolution (logMAR) units for the statistical analyses.

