### Interventions

Participants will be randomly divided into two arms in a 1:1 ratio. Surgery in two arms will be performed by qualified surgeons using the standard operating procedure of IOL implantation [1, 16].

After a conjunctival peritomy is made, a 3.2-mm superior scleral tunnel incision will be created. Sodium hyaluronate will be used to maintain the anterior chamber. Then, surgery will proceed in the different groups as per random allocation. All operations will be videotaped in their entirety.

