#### Secondary outcomes

The secondary outcomes include the following:Incidence of glaucoma-related AEs by 6 months, 3 years, 5 years, and 10 years postoperativelyIOL decentration by 6 months, 3 years, 5 years, and 10 years postoperatively.Incidence of other AEs by 6 months, 1 year, 3 years, 5 years, and 10 years postoperatively. Other AEs include IOL dislocation, iris synechia, corectopia and/or discoria, visual axis opacification, corneal endothelium decompensation, and retinal detachment. It will be recorded separately using criteria previously reported [22, 23].IOL tilt by 6 months, 1 year, 3 years, 5 years, and 10 years postoperatively.VA and ocular refractive power by 6 months, 1 year, 3 years, 5 years, and 10 years postoperatively.

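### The paired pre-to-post test of logMAR acuity makes no allowance for children who change acuity test between baseline and follow-up, so a change of test can be counted as a change in vision

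*Protocol article*

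**What the plan says.** The section on assessment of visual acuity sets the first-choice test: "Visual acuity will be evaluated with an Early Treatment Diabetic Retinopathy Study (ETDRS) chart". The fallback is chosen by ability: "For those who are unable to use the ETDRS chart, visual acuity is evaluated with Lea Symbol Chart or Teller Acuity Cards". There is no order of preference between the two fallbacks and no rule for a child whose test changes at a later visit. The same section then states: "All decimal visual acuity outcomes will be converted to logarithm of the minimum angle of resolution (logMAR) units for the statistical analyses".

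The inclusion criteria admit children from 18 months to 14 years. The general eligibility text sets the lower limit at 18 months for unilateral and 24 months for bilateral aphakia. Acuity is in the baseline examination and is a secondary outcome: "VA and ocular refractive power by 6 months, 1 year, 3 years, 5 years, and 10 years postoperatively".

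For the analysis, the Statistical methods section prescribes a t test for paired data, in these words: "test will be used to compare pre- vs. postoperative visual acuity (in logMAR), spherical equivalent aberration, IOL tilt, and decentration at each time point". For the randomised contrast it says: "Comparison between the two treatment groups will be performed using a mixed model for continuous outcomes". Neither sentence mentions the acuity test used.

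**The concern.** Teller cards ask whether a child detects a grating. Lea symbols and the ETDRS chart ask whether a child recognises a shape or letter. Conversion to logMAR gives these results a common unit but does not make them the same measurement. If a child is measured by grating before surgery and by recognition afterwards, the paired difference contains the offset between the tests as well as any change in the eye. Averaging over children does not remove this, because the change of test runs mostly one way: children gain the ability to use a chart as they grow.

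The trial is intended to inform clinical guidelines, and acuity is one of its named efficacy outcomes. A reported gain or loss in acuity after implantation, with a p-value from a paired test, could partly reflect a change of chart.

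**Working it through.** The protocol states no effect size, SD or sample size for acuity, so there is no figure to reproduce. The check has three steps.

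**1. Can the test change within a child?** Adding follow-up to the minimum entry age gives:

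| Visit | Youngest unilateral (18 months at entry) | Youngest bilateral (24 months at entry) |
|---|---|---|
| 6 months | 2.0 years | 2.5 years |
| 1 year | 2.5 years | 3 years |
| 3 years | 4.5 years | 5 years |
| 5 years | 6.5 years | 7 years |
| 10 years | 11.5 years | 12 years |

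A child who cannot use ETDRS at entry will in most cases be able to use a recognition test at the later visits. The age distribution at entry is not given, so the share of such children is unknown.

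**2. Size of the within-arm shift.** Let f be the share of eyes that change test and d the systematic offset between tests in logMAR. Both are assumptions. With no true change in the eye,

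shift in mean change = f × d.

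- Low end: 0.3 × 0.1 = 0.03 logMAR.
- High end: 0.5 × 0.4 = 0.20 logMAR.

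To see what this does to the paired t test, take 114 patients per arm less 20% loss (114 × 0.8, about 91), one eye per child, two-sided alpha 0.0492 and an assumed SD of change of 0.3. The SD including the test artefact is √(0.3² + f(1−f)d²), and the noncentrality is f·d divided by that SD over √91.

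| f | d | Shift | SD with artefact | Noncentrality | Rejection rate with no true change |
|---|---|---|---|---|---|
| 0.25 | 0.1 | 0.025 | 0.303 | 0.79 | 12% |
| 0.5 | 0.1 | 0.050 | 0.304 | 1.57 | 34% |
| 0.5 | 0.2 | 0.100 | 0.316 | 3.02 | 85% |

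The nominal rate is 4.92%. With an SD of 0.4 the first row falls to 9%.

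**3. Between-arm comparison.** Allocation is random: "Participants will be randomly divided into two arms in a 1:1 ratio". The expected mix of tests at any visit is therefore the same in both arms, and the expected shift in the difference is zero. What remains is extra variance. If a share p is on Teller cards at a visit, the variance is multiplied by

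1 + p(1−p)d²/SD².

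- p = 0.3, d = 0.1, SD = 0.4: 1 + 0.21 × 0.01/0.16 = 1.01.
- p = 0.5, d = 0.3, SD = 0.3: 1 + 0.25 × 0.09/0.09 = 1.25.
- p = 0.5, d = 0.4, SD = 0.3: 1 + 0.25 × 0.16/0.09 = 1.44.

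A Teller share of 30–50% is doubtful once the youngest child is 4.5 years old. The loss of precision therefore concerns mainly the 6-month and 1-year visits.

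**The case against.** The strongest reply is that the trial's question is untouched. Every stated objective compares in-the-bag with sulcus implantation, and none concerns pre-to-post change. This stands. A reader might infer from the mixed tests that the capsular-versus-sulcus contrast in acuity is biased. The documents do not support that, because assignment is random and the test is chosen by the child's ability.

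A reader might also infer that every child's test changes with age, or that a 10-year trend model is distorted. Neither is supported. Entry runs to 14 years, so children able to use ETDRS at entry may never change test. No trend model is specified, only a series of paired tests and a mixed model.

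It can also be said that the conversion sentence covers decimal acuities only and does not state that Teller results are pooled with chart results. That is fair: pooling is the natural reading, not a written rule. But the paired test is prescribed for logMAR acuity without exception, and nothing sets Teller results apart.

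Finally, covariates of a secondary model are commonly left to the SAP, and this is a condensed article. The absence of a test term from the mixed model is therefore not an error. The paired t test is different, because the article itself chooses that analysis.

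**Conclusion.** The point holds for the within-arm comparison. For children who enter too young for ETDRS, the prescribed paired test may subtract one kind of acuity from another and read the result as change. The shift is 0.03 to 0.20 logMAR for an assumed share of 30–50% and an assumed offset of 0.1–0.4. The protocol gives neither figure, nor the direction of the offset. In the illustration, even a mild case (a quarter of eyes changing test, offset 0.1, SD of change 0.3) more than doubles the rejection rate, from 4.92% to 12%.

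The between-arm comparison is unbiased in expectation and loses only precision, about 1% to 44% in variance under the assumptions shown, mainly in the first year. Acuity is a secondary outcome, and neither IOL decentration nor glaucoma-related adverse events is affected. This is a limited flaw that is cheap to correct.

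**What to change.** In the Statistical methods section:

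1. Label the paired pre-to-post acuity comparison descriptive. Report it separately for eyes measured with the same test at both visits and for eyes whose test changed, and interpret a numerical change only in the former.
2. Adjust the between-arm mixed model for acuity for age at secondary IOL implantation, which is already collected as history information, and for the acuity test used at baseline. Both are fixed before treatment, so adjusting for them keeps the randomised comparison intact.
3. Report grating and recognition acuity separately by arm, and add a recognition-only between-arm analysis at 3, 5 and 10 years as a sensitivity analysis.

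No new visit, device or participant is needed, only a record of the test used at each visit. The real cost falls on the late pre-to-post results. Same-test pairs become few at the later visits and over-represent children who were older at entry. Those changes will be imprecise, will describe a selected subgroup and will still include normal visual maturation. For that reason, restricting the whole pre-to-post analysis to same-test eyes would not be a sufficient remedy on its own.
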